### Randomisation and allocation

An administration assistant independent to the trial will prepare 441 sequentially numbered (1 to 441) opaque envelopes each containing an allocation card wrapped in extra paper or aluminium foil [56]. Allocation sequence is determined by a web-based computer generated (http://www.randomizer.org/) blocked random number table (7 blocks of 63; 1 = intervention, 2 = control). The randomisation tables are then sealed in an opaque envelope, locked within the research institute, and made unavailable to trial personnel. The number of consecutively numbered envelopes provided to each site will be dependent on funding agreements (that is, funded to recruit one block of 63 participants or, on a per patient recruit basis, until the end of the trial).

Local investigators will screen elective surgery and PAC lists daily for eligible patients who will be met face to face by local investigators at their PAC appointment. Informed consent will be obtained from potential participants; each eligible participant will be provided with a trial information sheet which is explained verbally to them and will be invited to participate. Those agreeing will sign a consent form as required by local ethics committees and in accordance with the Declaration of Helsinki. Where the local investigator or eligible patient is unable to attend PAC, the latter will be contacted by telephone and invited to enter the trial. The information and consent form will be mailed by post for signing, and the participant will be requested to bring them to hospital on the day of their operation.

Once informed consent has been obtained and the consent form signed, the pre-operative physiotherapist receives the group allocation for participants by opening the next sequentially numbered sealed opaque envelope containing the randomised group allocation. Patient details will be written on the envelope once opened to ensure that patients are randomised in the same order as recruited and the envelopes filed securely along with the consent form. Potential selection bias will be studied by extracting basic demographic data and planned surgical procedure from all excluded patients’ medical records.

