### Standardisation of pre-operative interventions

The information booklet content will remain consistent between participating centres, although the formatting may change for site-specific requirements. All participating pre-operative physiotherapists will be required to view a scripted audio-visual recording of the pre-operative intervention prior to recruiting their first patient. They are instructed to adhere to the overall themes and premises of information delivery as included within the protocol script and video. Years of experience, seniority grade, and numbers of participants seen by each physiotherapist will be reported.

Ideally, interventions will be provided in person at PAC within six weeks of the scheduled surgery. However, in keeping with a pragmatic approach, if an eligible patient or physiotherapist is unable to attend PAC, patients can be enrolled, randomised, and provided with the interventions on another convenient day, or via telephone, prior to surgery. The mode of delivery will be recorded and the total proportion of telephone sessions will be reported. If a participant’s operation is delayed and the time from Pre-Op physiotherapy to day of surgery becomes greater than 42 days, a physiotherapist will contact the participant by phone for a review assessment and to remind them to read the booklet as provided at PAC. Participants allocated to the intervention group will, in addition, have a review of the education session and the DB&C exercises repeated over the phone.

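### Patient details are written on the allocation envelope only after it is opened, so the step cannot secure allocation in recruitment order as intended

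*Protocol article*

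**What the plan says.** All of this is in the protocol article, mostly under Randomisation and allocation.

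- **Order of steps.** Opening follows consent and a signature on the form. At that point "the pre-operative physiotherapist receives the group allocation for participants by opening the next sequentially numbered sealed opaque envelope".
- **Recording the patient.** "Patient details will be written on the envelope once opened to ensure that patients are randomised in the same order as recruited". The opened envelopes are then filed with the consent forms.
- **Protection of the sequence.** An administrator independent of the trial prepares 441 numbered "opaque envelopes each containing an allocation card wrapped in extra paper or aluminium foil". The randomisation tables are sealed, "locked within the research institute, and made unavailable to trial personnel".
- **Telephone route.** When the patient or investigator cannot attend the clinic, the consent form is posted and "the participant will be requested to bring them to hospital on the day of their operation". Under Standardisation of pre-operative interventions, such "patients can be enrolled, randomised, and provided with the interventions on another convenient day, or via telephone, prior to surgery".

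**The concern.** The recording step has a declared purpose: to make sure that patients are randomised in the order in which they were recruited. To do that, it would have to fix the pairing of patient and envelope while the allocation is still unknown. As written, the pairing is recorded when the opener already knows the card. Until then the envelope belongs to nobody, so a card that has been seen could go to a different consenting patient.

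The trial relies on concealed allocation for its primary comparison of post-operative pulmonary complications (PPC). The Discussion also relies on effective random allocation to balance things that are neither measured nor controlled, such as walking outside the assisted sessions and breathing exercises led by ward staff. If patients were steered by perceived risk at this step, blinded outcome assessment would not repair the comparison, and covariate adjustment would correct only for measured factors.

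**Working it through.** **1. What each stated safeguard covers**

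| Safeguard | Hides the next card before opening? | Binds a named patient to the envelope before opening? |
|---|---|---|
| Independent preparation | Yes | No |
| Opaque envelope, wrapped card | Yes | No |
| Tables sealed and locked away | Yes | No |
| Envelopes used in number order | Not applicable | No: fixes which envelope is next, not whose it is |
| Consent and signature first | Not applicable | Partly: limits who can be paired, but names no envelope |
| Details written once opened | No | No: done after the card is seen |
| Filing with the consent form | No | No: a record after the event |

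No row answers yes in the last column. Two other provisions do not fill the gap. The selection-bias check draws on the records of excluded patients, so it does not compare arm with arm. The random covert audits under Data management check collected data against the medical record and do not mention envelopes.

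**2. Where the gap is widest**

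- *Patients consented at about the same time.* Exchanging their cards leaves envelope numbers and consent dates in agreement. Only recorded times could show it, and the article states none.
- *Telephone route.* The patient brings the signed form on the day of the operation, but randomisation and the session take place before surgery. The site therefore need not hold a signed form when the envelope is opened, so the consent-first safeguard is weakest here.

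**3. Figures in the plan**

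The point does not depend on the sample size, but the figures reproduce. For 20 % versus 10 %, two-sided 0.05 and 80 % power, the requirement is 199 per arm, 398 in total. With the 11 % increase, 398 × 1.11 = 441.8, against 441 stated; 7 blocks × 63 = 441 envelopes. Changing when the details are written alters none of these.

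**4. Illustration of size**

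Inputs from the article: 441 participants, so about 220 per arm (441 / 2 = 220.5); PPC rates from the Discussion of about 40 % in high-risk patients and 13–18 % across all types of surgery; target difference 20 % − 10 % = 10 points (Sample size).

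Assumptions not in the article: the number of swaps k; every swap runs in the same direction; each exchanges one patient at 40 % risk with one at risk p; the analysis is unadjusted.

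One swap lowers expected risk in one arm by (0.40 − p)/220 and raises it by the same amount in the other, so

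shift in risk difference = 2k(0.40 − p)/220.

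| Swaps k | Patients involved | p = 0.18 | p = 0.13 |
|---|---|---|---|
| 5 | 10 (about 2 %) | 10 × 0.22/220 = 1.0 point | 10 × 0.27/220 = 1.2 points |
| 11 | 22 (about 5 %) | 22 × 0.22/220 = 2.2 points | 22 × 0.27/220 = 2.7 points |
| 22 | 44 (about 10 %) | 44 × 0.22/220 = 4.4 points | 44 × 0.27/220 = 5.4 points |

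A handful of swaps matters little. Steering of about one participant in ten, all one way, would amount to roughly half the target effect.

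**The case against.** The strongest reply is that the scheme is concealed where it matters most. The opener cannot foresee the next card, consent comes first, and moving a seen card on the face-to-face route needs a second consented patient who has not yet been randomised, or a breach of the stated order. The article does not say how often two such patients coincide. Numbered envelopes filed with consent forms also leave evidence: a skipped envelope shows as a gap or a late-used number, and an exchange across days shows as a mismatch between envelope order and consent order. The planned assessment of baseline imbalance and the adjusted analyses might reveal or absorb part of any risk-based steering.

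This stands as a limit on severity. It does not rescue the sentence, which still claims to ensure an order that it can only record.

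A reader might infer more than the documents support:

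- *That allocation was or will be subverted, or that concealment is absent.* Nothing in the article shows this. One step is weak.
- *That tampering would leave no trace.* Disorder across days would leave a partial one. Exchanges on the same day would be hard to detect.
- *That the opener has already met and assessed the patient.* The article has local investigators meet patients and the pre-operative physiotherapist open the envelope. It does not say whether the assessment precedes opening, or that the opener then knows the patient's risk stratum.
- *That the shifts, or an inflated type I error derived from them, are estimates for this trial.* They follow from assumed swap counts that all run in one direction.

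**Conclusion.** The point holds as a procedural vulnerability. The article fixes the time of writing explicitly, so this is not a detail left to a fuller document, and that timing cannot achieve the purpose given for it. No other stated step binds patient to envelope before the allocation is seen.

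The size cannot be estimated from the documents. Under the one-directional, unadjusted assumptions above, 5 to 22 swaps would shift the risk difference by about 1 to 5 points against a target of 10; with few or no swaps the effect is negligible. Given the other safeguards and the partial audit trail, this is a recommended cheap improvement and not a must-fix.

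**What to change.** Replace the sentence with wording such as:

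> After consent, and before the envelope is opened, the participant's identifier, the date and time, and the opener's signature are written on the sealed envelope and entered in a consecutive site log. The allocation inside then belongs to that participant.

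Existing trial personnel then check envelope numbers against consent dates and times and report any envelope that is missing or out of sequence. For the telephone route, the log should also show when consent was given and whether the signed form was in hand at opening.

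The cost is one log entry per participant and the time for the check. The envelopes already prepared can be used, and no sample size, power or significance figure changes. The limitation is that allocations already made can only be audited, not protected. The Trial status section says that enrolment is continuing, so the change would still protect the remaining allocations.

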### Trial interventions

Consenting participants will be randomly assigned to receive either i) a pre-operative assessment from a physiotherapist and provision of an information booklet (control) or ii) an additional education and DB&C training session (intervention).

### Control group

Participants will have a standardised assessment conducted by a physiotherapist consisting of: questioning on current health co-morbidities, mobility and functional status, smoking history, lung auscultation, subjective assessment of cough quality and strength, sputum production and colour, hand grip strength, Rapid Assessment of Physical Activity (RAPA) [57] and Specific Activity Questionnaire (SAQ) [58] to determine current activity and fitness levels, and Short Form 36 (SF-36 V2) [59] to measure HRQoL (see Data Collection section for further details). Participants will then be provided with an education booklet. This colour booklet contains written and pictorial information about abdominal surgery, expected types of pain management, medical lines and drains, post-operative recovery process, and how to prevent post-operative respiratory complications with early ambulation and self-directed DB&C exercises. The booklet includes detailed written instructions to perform DB&C exercises for two sets of 10 deep breaths followed by three coughs every hour during waking hours. Participants will be instructed to bring the booklet to hospital for reference following the operation. The contents of the booklet will not be discussed with participants in the control group and there will be no additional physiotherapy provided pre-operatively.

### Intervention group

Intervention group participants will be assessed and provided with an information booklet as per the control group and will then receive an additional single education and training session of approximately 30 min with a physiotherapist. Participants will be given an estimate of their likelihood of a PPC based on a risk prediction tool [5] and educated about the effect of anaesthesia, UAS, and bed rest on mucociliary clearance and lung volumes [19, 20]. To ameliorate these factors and prevent bacteria stagnation [15, 16] the importance of participating in an early post-operative ambulation program and performing self-directed DB&C exercises will be emphasised. Participants will be informed that a physiotherapist will assist them to walk as soon as possible on the first post-operative day, aiming for a duration longer than 10 min and at a pace causing mild breathlessness. Outside these assisted sessions, participants will be advised to walk or exercise by their bedside as frequently as they are able.

As it is frequently not possible to ambulate as early and as often as recommended to assist in preventing respiratory complications [8, 60], participants will be educated on the necessity of performing self-directed breathing exercises to protect their lungs following their operation. They will be instructed to perform DB&C exercises immediately from waking from the anaesthetic and then every hour during daytime waking hours until their first ambulation session, and then at any time when they are not ambulant. The physiotherapist will coach each participant in at least three repetitions, and as many as required to master technique as judged by the physiotherapist. This trial’s DB&C exercises consist of two sets of 10 slow-flow breaths to maximum inspiratory capacity with two to three inspiratory sniff breath stacking manoeuvres [61]. Each breath is held for 3 to 5 s. Each set of 10 breaths is followed by three coughs, or a forced expiratory technique with an open glottis called a ‘huff’, with a small firm pillow pressed over on the abdominal incision to support the wound and to encourage greater expiratory force. Participants will be encouraged to practice these exercises prior to their operation to develop familiarity.

### Standardisation of pre-operative interventions

The information booklet content will remain consistent between participating centres, although the formatting may change for site-specific requirements. All participating pre-operative physiotherapists will be required to view a scripted audio-visual recording of the pre-operative intervention prior to recruiting their first patient. They are instructed to adhere to the overall themes and premises of information delivery as included within the protocol script and video. Years of experience, seniority grade, and numbers of participants seen by each physiotherapist will be reported.

Ideally, interventions will be provided in person at PAC within six weeks of the scheduled surgery. However, in keeping with a pragmatic approach, if an eligible patient or physiotherapist is unable to attend PAC, patients can be enrolled, randomised, and provided with the interventions on another convenient day, or via telephone, prior to surgery. The mode of delivery will be recorded and the total proportion of telephone sessions will be reported. If a participant’s operation is delayed and the time from Pre-Op physiotherapy to day of surgery becomes greater than 42 days, a physiotherapist will contact the participant by phone for a review assessment and to remind them to read the booklet as provided at PAC. Participants allocated to the intervention group will, in addition, have a review of the education session and the DB&C exercises repeated over the phone.

### Standardisation of post-operative procedures

At the first available opportunity following surgery, all participants will be seen by a physiotherapist for a standardised assisted ambulation session (see Table 3). Ambulation is defined as marching on the spot beside the bed or walking away from the bedside for more than 1 min. Once a patient is ambulant for more than one minute, an Allied Health Assistant (AHA) will conduct all further ambulation sessions. If an AHA is unavailable, then a physiotherapist will continue to provide assisted ambulation. Health professionals (profession and years of experience) delivering ambulation will be reported. Participants will be seen once daily until discharged from physiotherapy services using defined scoring criteria [62] (see Table 4) or until discharged from hospital.

**Table 3 Tab3:** LIPPSMAck POP ambulation protocol

Stage 1 (Safety)	Sit over edge of bed/sit in chair minimum of 2 min
Stage 2 (Safety)	March on spot 0–1 min
Stage 3 (Ambulation)	March on spot/walk away from bedside 1–3 min
Stage 4 (Ambulation)	March on spot/walk away from bedside 3–6 min
Stage 5 (Ambulation)	Walk away from bedside 6–10 min
Stage 6 (Ambulation)	Walk away from bedside 10–15 min
Stage 7 (Ambulation)	Walk away from bedside >15 min

**Table 4 Tab4:** Discharge from physiotherapy scoring tool [62]

Mobility	Score
Reached pre-operative ambulation status	3
Requires supervision, status has plateaued	2
Requires assistance, status is improving	1
Unable to ambulate	0
Breath sounds	
Reached pre-operative levels and within expectations for that patient	3
Slightly decreased breath sounds or presence of a few added sounds	2
Markedly abnormal breath sounds and/or significant added sounds	1
Secretion clearance	
Able to clear secretions independently OR at pre-operative status	3
Requires assistance to clear secretions	1
SpO_2_% (on room air or pre-op oxygen levels)	
SpO_2_ ≥ 92 % (no respiratory condition) OR SpO_2_ ≥ 88 % (existing respiratory condition)	3
SpO_2_ < 92 % (no respiratory condition) OR SpO_2_ < 88 % (existing respiratory condition)	2
Respiratory rate (at rest and during activity)	
Within normal expectations	3
Outside acceptable range for the individual	2
Total score (min 6, max 15)	
A score ≥14 = discharge from physiotherapy	

At each session the participant will be progressed sequentially through the ambulation protocol stages aiming to achieve a walking time of more than 10 min at an intensity of at least three on the Borg 10-point visual analogue scale of perceived exertion [63] and where breathing is deeper than at rest. If necessary, ambulation sessions can comprise intervals at a work/rest ratio of 1:1. Shorter, but not longer, rest times are allowable. The final achieved ambulation stage is the total amount of time walked, not including rest periods. If participants are unavailable or unable to achieve ambulation for more than 1 min, the assisted ambulation session will be attempted again later in the day. Reasons will be recorded where participants are unable to ambulate or do not achieve a minimum of 10 min walking. Physiotherapists and AHAs will be provided with protocol prompt cards and trained by the site investigator.

At the first ambulation session participants will be provided with a walking aid if required, an abdominal support pillow for use during coughing, and a brief reminder to perform DB&C exercises as described within the information booklet provide pre-operatively. If a participant has forgotten his/her booklet, a new one will be provided. Participants will be encouraged to ambulate frequently to aid in the prevention of PPCs and encouraged to seek assistance from a nurse if necessary and to walk with their visitors. There will be no further provision of DB&C, PEP devices, incentive spirometers, or NIV by physiotherapists or AHAs.

Additional ambulation occasions outside physiotherapy assisted sessions or other ward staff encouraging patients to perform respiratory exercises will not be measured or controlled, as this would not be feasible. Both are considered standard ward care for both control and intervention group participants. However, if a participant is provided with an incentive spirometer or PEP device, this will be immediately removed. The break to protocol and duration of access to device will be recorded.

All other aspects of patient care, including pre-operative preparation, general anaesthesia, intraoperative ventilation parameters, fluid delivery, prophylactic antibiotic prescription, pain management, use of lines and drains, general nursing care, and discharge planning, will be provided at the discretion of nurses and physicians according to routine clinical practice at each participating centre.

### Blinding

Pre-admission clinic nurses and physiotherapists aware of group allocation will not have contact with participants post-operatively. A trial participation sticker (excluding group allocation) will be placed in the medical record. All post-operative ward staff, physiotherapists, PPC assessors, doctors, surgeons, nurses, discharge planners, data analysts, and statisticians will be blinded to group allocation. If a treatment group participant informs the assessor of their pre-operative education session, this will be noted and reported.

It is anticipated that patients will consider the pre-operative physiotherapy assessment and provision of a booklet an acceptable ‘sham’ treatment. This will be measured by interviewing a convenience sample of 30 consecutive participants via a semi-structured interview on their fifth post-operative day, or on the day of discharge, whichever comes first. They will be asked which group they believed they had been allocated to and, to test fidelity of the intervention over the control, what they remembered from their pre-operative physiotherapy session. The success of participant and therapist blinding will be tested and reported by requiring post-operative physiotherapists, AHAs, and assessors to guess group allocation for each of these 30 participants.

### Withdrawal from trial

Participants will be withdrawn for either of the following: (i) failure to progress to surgery within the first 3 months of PAC attendance or (ii) withdrawal of consent. All withdrawals and reasons will be reported.

